Research on gut microbiota and the key determinants of microbial variation among Southeast Asian children remains lacking (52). Specifically, the Malaysian Working Group on Gastrointestinal Health reported a lack of research and awareness on the role of gut microbiota in early life (53). Increased awareness on the importance of gut health will help establish pre-natal and post-natal factors that promote healthy development and functioning of the immune system, gastrointestinal health, and metabolism in infants. In Malaysia, previous studies on gut microbiota mainly focused on pre-adolescent (52, 54) and pre-school children (55). While there are few local mother-infant cohort studies (45, 56, 57), none observed changes in infant gut microbiota over time.

Overall, it is essential to understand the host-microbe interactions in the first year of life since this period is crucial for infant health programming and may influence infant development with short- and long-term health consequences (1–3). The lack of evidence, especially from the Southeast Asia, calls for further studies to understand how gut microbiota in early life affects disease development (allergy, eczema, metabolic disease, and gastrointestinal disease) into adulthood. Since there is a lack of longitudinal research on infant gut microbiota in Malaysia, this cohort study aims to determine the association between gut microbiota with infant health (temperament, gastrointestinal disorders, eczema, asthma, and developmental delays) during the first year of life at different follow-ups. The specific objectives include:

To assess infant gut microbiota (composition, taxonomy, diversity, and abundance) during the first year of life.To assess temperament, gastrointestinal disorders, eczema (presence and severity), asthma (likelihood of developing), and developmental delays of infants.To determine the associations between socio-demographic, pre-natal and post-natal factors with gut microbiota in infants at 12 months.To determine the associations between infant gut microbiota and infant health (temperament, gastrointestinal disorders, eczema, asthma, and developmental delays) at 12 months.

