#### Questionnaires

A set of validated questionnaires will be used to collect information at different time points as the following:

Physical activity: Pregnancy Physical Activity Questionnaire (PPAQ) (72);Food security: Six-item U.S Department of Agriculture (USDA) Food Security Survey Module (FSSM) (73);Stress during pregnancy: Perceived Stress Scale (PSS)-10 (74);Depression: Edinburgh Postnatal Depression Scale (EPDS) (75);Gastrointestinal disorders of infants: Rome IV Diagnostic Questionnaire for Pediatric Functional Gastrointestinal Disorders-Toddler (R4PDQ-Toddler) (76);Infant temperament: Revised Infant Behavior Questionnaire (IBQ-R) (77);Presence of eczema in infants: five questions of the UK Working Party's Diagnostic Criteria for Atopic Dermatitis (78);Severity of eczema symptoms in infants: Patient-Oriented Eczema Measure (POEM) for children (79);Asthma symptoms in infants: Asthma Predictive Index (API) (80);Appetite traits: Baby Eating Behavior Questionnaire (BEBQ) (0–5 days, 10–15 days and 1 month) (81) and Children Eating Behavior Questionnaire (CEBQ) (4, 6, and 12 months) (82);Developmental delays: Ages and Stages Questionnaire, third edition (ASQ-3) (83).

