### Statistical analysis

The IBM SPSS Statistics software version 27 (IBM Corp., Armonk, NY, USA) will be used to analyze the data. Categorical variables will be presented in frequency and percentage, while continuous variables are presented as mean ± standard deviation (SD). The normality of continuous data will be tested using the skewness test (89). Gut microbiota will be analyzed in terms of alpha diversity, beta diversity, and differential abundance of OTUs (87). The incidence rates of asthma, eczema and gastrointestinal disorders among infants will also be calculated. Principal coordinate analysis (PCoA) plots with phylogenetic and non-phylogenetic distances will be plotted (87). One-way ANOVA with corrections (Bonferroni method) and Tukey HSD test will be carried out (89) to test for statistically significant differences in taxonomic richness, diversity measures, bacterial load, and bacterial abundances. Permutational multivariate analysis of variance (PERMANOVA) based on Bray–Curtis distances and 1,000 permutations (89) will be used to evaluate which factors are associated with the composition of the microbiota.

A generalized linear model (GLM) will be used (90) to determine the associations between predictors and gut microbiota and the association between gut microbiota and infant health after controlling for confounders. The strength and precision of each association will be determined using the relative risk (RR) with 95% confidence intervals (CI) after adjusting for potential confounders. The significance level for all statistical analyses will be set at *p* < 0.05. Meanwhile, the Bonferroni correction will be applied to counteract the effect of multiple testing and avoid multiple spurious positives (91). The alpha value will be adjusted to account for the number of comparisons performed (91).

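### The plan fixes a relative risk for each association, but this measure is undefined for the gut microbiota outcomes of objective 3 and for temperament and eczema severity if these are analysed as scores

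*Protocol article*

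**What the plan says.** In the Statistical analysis section of the protocol article, a generalized linear model is assigned to two sets of associations: "to determine the associations between predictors and gut microbiota and the association between gut microbiota and infant health after controlling for confounders". The next sentence sets the effect measure for both: "The strength and precision of each association will be determined using the relative risk (RR) with 95% confidence intervals (CI". It makes no exception.

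The first set of associations is objective 3, at the end of the Introduction: "To determine the associations between socio-demographic, pre-natal and post-natal factors with gut microbiota in infants at 12 months". Objective 1 describes the form of the microbiota data: "To assess infant gut microbiota (composition, taxonomy, diversity, and abundance) during the first year of life". The Statistical analysis section says how they will be handled: "Gut microbiota will be analyzed in terms of alpha diversity, beta diversity, and differential abundance of OTUs".

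The second set is objective 4, on infant health. The Questionnaires section lists the instruments, among them "Infant temperament: Revised Infant Behavior Questionnaire (IBQ-R) (77") and POEM for eczema severity. It gives no cut-off for either.

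**The concern.** The exposure in a relative risk may be of any type, but the outcome must be an event that an infant has or does not have. In objective 3 the microbiota is the outcome, and none of its planned forms is an event. The rule therefore names a measure that cannot be computed for that objective as the data are described.

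An analyst who follows the sentence must dichotomise diversity, abundance and scores at cut-points that the article does not give. That discards information. If the cut-points are chosen after the data are seen, it also adds analytic freedom across many taxa and outcomes. An analyst who does not follow it departs from the published rule.

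**Working it through.** **1. Outcomes set beside the rule**

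| Outcome | How the article describes it | RR defined as written? |
|---|---|---|
| Alpha diversity (obj. 3) | Diversity measures compared by one-way ANOVA and Tukey HSD, so as means | No |
| OTU abundance (obj. 3) | Abundances compared in the same way | No |
| Beta diversity/composition (obj. 3) | Bray–Curtis distances, PERMANOVA, PCoA | No |
| Temperament (obj. 4) | IBQ-R; individual differences in behaviour (Introduction); no cut-off | Not if analysed as a score |
| Eczema severity (obj. 4) | POEM; no cut-off | Not if analysed as a score |
| Gastrointestinal disorders, eczema presence, asthma (obj. 4) | Incidence rates to be calculated | Yes |
| Developmental delay (obj. 4) | Named as a delay, measured by ASQ-3 | Yes, if classified yes/no |

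The same section thus compares diversity and abundance as means and then promises a relative risk for them.

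**2. The plan's own sample size**

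Inputs from Participant selection: effect size 0.427, 95% confidence, 80% power, 29.0% attrition, 225 pairs. Assumption: 0.427 is a standardized difference between two means and the test is two-sided, since the article does not state the type of effect size.

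- Per group: n = 2 × (1.960 + 0.842)² / 0.427² = 2 × 7.849 / 0.1823 = 86.1, so 87.
- Total: 174. Then 174 × 1.29 = 224.5, so 225, which matches.
- Reading 0.427 as a relative risk, with the Introduction's 27.6% (eczema), 10.5% (regurgitation) or 6.1% (wheezing) as the comparison risk, gives at least 198 before attrition and at least 256 after the same inflation. This does not match.

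The stated size therefore fits a comparison of means, for which a relative risk is undefined. This is supporting evidence only, because the effect size type is inferred.

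**3. Illustration: the cost of forcing a relative risk**

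The article plans no median split. It is assumed here only to show scale, for a normal outcome.

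- Information kept: 2/π = 0.637, about 64%.
- Power of a test that had 80%: Φ(2.802 × √0.637 − 1.960) = Φ(0.276) = 0.61.
- Direct check with d = 0.427: the proportions above the split are Φ(0.2135) = 58.5% and 41.5%, so RR = 58.5 / 41.5 = 1.41.
- With 87 per group, power falls from 80.4% (means) to 60.8% (proportions).
- The total for 80% power rises from 174 (means) to 274 (137 per group), before attrition.
- With 80 per group (225 × 0.71 ≈ 160 pairs left after 29% loss), power falls from 77.1% to 57.2%.

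**The case against.** The strongest reply is that this is one over-general sentence in a condensed article. The section does not leave objective 3 without a method: ANOVA and Tukey cover diversity and abundance, PERMANOVA covers composition, and the GLM can give ordinary coefficients for continuous outcomes. Cut-offs and link functions may properly sit in an analysis plan that is not shown.

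Much of this stands. It would be too strong to say that the plan yields no valid estimate for objective 3. But ANOVA does not supply the adjusted effect measure that the sentence promises. The sentence also does more than omit detail: it fixes the measure for each association. Cut-points in an analysis plan would make a relative risk computable for single scores, at the cost shown above. They would not directly help beta diversity, which is a distance between samples. Nor does a loose reading of the term help: a log link for abundance gives a ratio of means, not a relative risk.

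Three stronger readings are tempting, and the document does not support them:

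- **The measure fails for most of the plan.** Four objective 4 outcomes (gastrointestinal disorders, eczema presence, asthma, developmental delay) admit a relative risk. A majority appears only if composition, taxonomy, diversity and abundance are counted as separate outcomes.
- **Odds ratios will be reported as relative risks.** The article names neither a logit link nor an odds ratio. A GLM with a relative risk is consistent with a log link.
- **ASQ-3 is a continuous outcome.** The article names the outcome as developmental delays, which can be classified yes/no.

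**Conclusion.** The sentence is wrong as written and should be fixed. A relative risk is undefined for all the microbiota outcomes of objective 3. It is also undefined for temperament and eczema severity if they are analysed as scores. That condition is needed because the article does not describe IBQ-R or POEM scoring. For temperament, a score is inferred from its description, the lack of a cut-off, and its absence from the outcomes given incidence rates.

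The figures of about 64% of the information and about 61% power rest on a normal outcome split at the median. They show what a literal reading could cost and do not predict what the investigators will do. The defect lies in the reporting rule and does not touch data collection or the sample size.

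**What to change.** Replace the sentence with effect measures by outcome type:

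- **Alpha diversity, abundance, temperament and eczema severity scores:** adjusted mean difference, or ratio of means under a log link, with 95% CI. Any transformation of abundance can be left to the analysis plan.
- **Composition and beta diversity:** R-squared and p from the PERMANOVA already planned.
- **Binary health outcomes only (gastrointestinal disorder, eczema present, API-positive, developmental delay):** adjusted relative risk with 95% CI, from a model that estimates it directly, such as a log-link Poisson GLM with robust standard errors.

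If any score is to be dichotomised, the cut-point and its reason should be stated before the data are analysed. The cost is wording in the analysis section or analysis plan. No visit, sample, instrument or recruitment target changes.

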### Participant selection

The sample size required for this cohort study is 225 mother-infant pairs, considering the effect size of 0.427 (59), confidence level of 95%, power of 80% and attrition rate of 29.0% (45). First, the list of private hospitals in Selangor will be obtained from the Ministry of Health. Next, eight private hospitals will be randomly selected using a computerized random number generator with an estimated participation of 30 eligible pregnant women per hospital in a month. Pregnant women aged between 18 and 45 years old in their first trimester of pregnancy who visit the selected private hospitals and plan to attend post-natal check-ups for at least 1 year in the study area will be recruited. Meanwhile, pregnant women diagnosed with immune deficiency, severe allergic conditions, psychiatric disorders, multiple pregnancies, preterm delivery (<37 weeks), a newborn with congenital abnormalities, and hospitalized in neonatal intensive care unit immediately after birth will be excluded from this study.

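### The sample size of 225 matches one unadjusted test, but the plan promises Bonferroni over a family that it does not fix in advance

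*Protocol article*

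**What the plan says.** All statements are in the protocol article.

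- **Introduction, specific objectives.** The fourth objective is "To determine the associations between infant gut microbiota and infant health (temperament, gastrointestinal disorders, eczema, asthma, and developmental delays) at 12 months". The five outcomes stand side by side; none is called primary or ranked. The third objective is a separate search for factors associated with the infant microbiota.
- **Participant selection.** The 225 pairs are derived by "considering the effect size of 0.427 (59), confidence level of 95%, power of 80" per cent, with 29.0% attrition. The effect size is attached to no outcome, microbiota measure or visit.
- **Statistical analysis, features and models.** "Gut microbiota will be analyzed in terms of alpha diversity, beta diversity, and differential abundance of OTUs". A generalised linear model is then used "to determine the associations between predictors and gut microbiota and the association between gut microbiota and infant health after controlling for confounders".
- **Statistical analysis, error control.** "The significance level for all statistical analyses will be set at *p* < 0.05". The text continues that "the Bonferroni correction will be applied to counteract the effect of multiple testing and avoid multiple spurious positives", and closes with "The alpha value will be adjusted to account for the number of comparisons performed". It gives no count, and does not say whether the correction runs per outcome, per objective, per class of feature or over the whole study.

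**The concern.** Two parts of the article do not fit together. The sample-size paragraph describes power for one comparison. The analysis section promises a stricter threshold for an unspecified number of comparisons. A reader who takes the 80% at face value will expect the study to detect its design effect in its main analysis with that probability, and it will not once the promised correction is applied.

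The family is also open. Its size depends on choices still to be made: which microbiota measure is used, how each health outcome is reduced to an endpoint, and whether individual taxa are counted. The number of operational taxonomic units (OTUs) is not known until sequences have been clustered (Microbiome analysis). Two analysts following the text faithfully could count different families and reach opposite conclusions from the same p-value.

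**Working it through.** **Inputs from the article.** Effect size 0.427, 95% confidence, 80% power, 29.0% attrition and 225 pairs (Participant selection); significance level 0.05 (Statistical analysis); five health outcomes (Introduction).

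**Assumptions.** 0.427 is a standardised mean difference between two equal groups, and tests are two-sided. The article states neither. They are adopted because they reproduce its figure. A normal approximation is used throughout.

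**Step 1: reproduce 225.**

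- Per group: n = 2 × (1.960 + 0.842)² / 0.427² = 86.1, rounded up to 87, so 174 in total.
- Attrition added as a multiplier: 174 × 1.29 = 224.5, rounded up to 225. This matches.
- Readings that do not match: dividing by 0.71 gives 174 / 0.71 = 246; a one-sided test gives 68 per group; treating 0.427 as a correlation gives about 41 in total.
- With Bonferroni for five tests the same method needs 129 per group, and 258 × 1.29 = 333. So 225 contains no allowance for multiplicity.

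**Step 2: evaluable pairs.** 225 × 0.71 = 159.75, or about 80 per group.

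**Step 3: power at the corrected threshold.** The expected z-statistic is 0.427 × √(79.875 / 2) = 2.70. Power for m tests is Φ(2.70 − z), where z is the two-sided critical value at 0.05/m.

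| Tests counted (m) | Threshold | Power, about 160 evaluable |
|---|---|---|
| 1 | 0.05 | 77.0% |
| 5 (one per health outcome) | 0.01 | 54.9% |
| 15 (5 outcomes × 3 feature classes, illustrative) | 0.0033 | 40.6% |
| 100 (OTU level, illustrative) | 0.0005 | 21.7% |

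The first row is below 80% because adding 29% to 174 does not leave 174 after a 29% loss. The further drop to 55% comes from the correction alone. Five is the least that one test per outcome allows: eczema, for example, is assessed for both presence and severity.

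**Step 4: sensitivity to equal groups.** If the groups were infants with and without a condition, at the prevalences in the Introduction, power would be lower. For eczema at 27.6% it is 67% with one test and 44% with five. For wheezing at 6.1% it is 25% and 10%. Equal groups are therefore the favourable case.

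**Step 5: one p-value, two conclusions.** A result of p = 0.006 is significant while 0.05/m exceeds 0.006, that is up to m = 8 (0.05 / 0.006 = 8.3). It is positive at m = 5 (0.01) and negative at m = 15 (0.0033).

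**The case against.** The strongest reply is that alpha, method and principle are all stated, that the wording is an ordinary description of Bonferroni, and that listing the family belongs in an analysis plan that is not shown here. Much of this stands. Bonferroni over every test performed controls the family-wise error, and the absence of a list would not by itself be a finding in a condensed article. What remains is a conflict within the stated text: a power figure for one unadjusted test beside a promise to adjust.

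It can also be said that the source cited for 0.427 may identify the comparison. It may, but that would not restore 80% power at a corrected threshold.

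Several stronger readings are tempting and are not supported:

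- *The threshold will be chosen after results are seen.* The article does not say so. It leaves the count open, which permits this but does not plan it.
- *False positives will be common, for example 42% over 20 tests at correlation 0.5.* That figure assumes uncorrected testing at 0.05, whereas the article promises correction.
- *The family runs to 120 tests across six post-natal visits.* The fourth objective is fixed at 12 months. A count of 20 (five outcomes by the four features in the first objective) is likewise only an illustration, since that objective is descriptive.
- *Every association is affected alike.* The ANOVA comparisons carry their own Bonferroni and Tukey corrections; the point applies most directly to the generalised linear models and the OTU-level tests.

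**Conclusion.** The point holds in this form: the sample size is consistent with one two-group test at unadjusted two-sided 0.05, the analysis corrects for an unfixed number of tests, and the stated 80% power does not survive that correction. With about 160 evaluable pairs, power is about 77% for one test, 55% for five and 41% for 15. The conclusion on a result such as p = 0.006 turns on the count.

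The sizes rest on reading 0.427 as a standardised mean difference with equal groups. That reading reproduces 225 but is not stated. The counts of 15 and 100 are illustrative; five follows from one test per listed outcome. The article does not support a claim that its error control is invalid. This should be corrected, but it does not undermine the cohort or its data collection.

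**What to change.** 1. Before microbiota data are linked to health outcomes, fix the confirmatory family for the fourth objective: one named microbiota measure against one named endpoint for each of the five outcomes, at 12 months. Replace the open-ended divisor with that pre-listed size.
2. Control this family at 0.05 with Holm instead of Bonferroni. Holm gives the same family-wise control and is never less powerful. Under the assumptions above, power for any one outcome would lie between 55% (threshold 0.01) and 77% (threshold 0.05). Alternatively, name one outcome primary, test it first at 0.05, and test the other four with Holm only if it is significant. The gate matters: a primary test at 0.05 beside an ungated Holm family at 0.05 would let the error across the five outcomes reach about 10% (1 − 0.95² = 9.75% if independent).
3. Treat the third objective and the OTU-level tests as separate pre-defined families, each with its own correction. Label other visits and other microbiota features exploratory.
4. In Participant selection, state which comparison 0.427 refers to and restate the power at the adjusted alpha.

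The cost is a few sentences, with no extra pairs, samples or visits. Results outside the listed families carry no confirmatory claim, and the stated power becomes less favourable.

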## Discussion

Knowledge regarding the numerous contributions of the gut microbiota on human health is limited, and a lot remains to be discovered. Recent cohort studies have shown that gut microbiota is associated with temperament during infancy, which refers to biologically-based individual variation in behavior in the form of activity, affectivity, and self-regulation (31, 32). Moreover, alterations and instability of the gut microbiota composition and biodiversity during infancy could lead to the development of gastrointestinal disorders (34), eczema (35), asthma (24, 36, 42, 43), and developmental delays (37, 38).

The rising attention of good gut health development in infants to ensure optimal child development in Malaysia (52–55) necessitates this prospective cohort study. The major contributions of this study would include the prospective cohort study design and providing clarity of temporal sequence between exposures and outcome. This study involves comprehensive and prospective quantitative assessments of mothers and infants. Besides, frequent collections of urine, feces, saliva, and breast milk samples enable a holistic assessment of maternal and infant gut microbiota over time, identifying the microbiota alterations and abundance. However, one of the limitations of this study is the multiple assessments on the pregnant women during their first, second and third trimesters until 12 months postpartum, which could be potentially burdening and lead to high dropout rates. The commitment required in the collection and delivery of bio-samples in the morning may be burdensome for working mothers. These situations will be addressed by providing incentives per visit and a summary of findings and reminders about all the follow-up activities *via* phone calls and text messages. Another possible limitation is the compliance of mothers and infant sample collections (saliva, feces, urine, and breastmilk). This limitation will be overcome using user-friendly self-collection kits with clear instructions and reminders by the researchers. Furthermore, the researchers will collect samples, thus easing the burden of respondents. Besides, there are concerns on the response and social desirability bias due to the self-report nature of the questionnaire on infant health, including temperament, gastrointestinal disorders, eczema, asthma, and developmental delays. Moreover, differences in sample handling protocols, collection procedures and processing data pipelines could be the limitation of this study.

In general, the launching and implementation of this cohort is challenging, including challenges in logistic and methodological issues such as recruitment, retention, and data collection (92, 93). The common issue in the stage of launching the cohort is that it requires allocation of human resource with training provided to the researchers and enumerators to ensure proper handling of bio-samples (92, 93). During the recruitment stage, a liaison person can be assigned to build up rapport with the respondents and to perform the follow-ups in order to address respondents' concerns about their commitment required for the whole study duration, lack of interest and reluctance to enroll in the study before obtaining the husband's approval (92). Any cases involving lack of interest or husband's reluctance should be dealt with communication and inclusion of husbands in research arrangements to raise their awareness on the importance of their wife participation in the cohort. Importantly, ethical concerns involved in conducting a birth cohort must be carefully considered (93). Besides, the necessary start-up time, staff, and costs must not be underestimated (92). Moreover, additional costs relating to logistic and other expenses must be taken into consideration (92, 93).

The study findings could provide a better understanding of the colonization and development of the gut microbiome during early life. Furthermore, identifying the pre- and post-natal factors contributing to infant gut microbiota helps to fill the current knowledge gap on infant gut health. These findings could help stakeholders such as policymakers and healthcare professionals to develop appropriate educational and intervention programs to address pre- and post-natal factors that cause poor gut health among infants. Such initiatives could reduce the occurrence of preventable NCDs among infants and the financial burden on their families. Moreover, the findings of this study are useful in addressing modifiable risk factors that may impact infant gut microbiota. Suitable lifestyle, environmental, and dietary adjustments could be implemented to strengthen infants' immunity, cognition, and digestion. In summary, the gut-brain axis is a global concern and good gut health maintenance among infants is crucial in ensuring beneficial bacterial composition, diversity, and abundance in early life.

